## Methods and design

### Sample

Cases and controls will be identified through an epidemiologic survey conducted in the city of São Paulo. Details of the epidemiologic study are presented in a companion paper (cite) and are summarized here. To identify trauma victims in the community, interviews were conducted by a professional team specialized in household surveys, the Brazilian Institute of Public Opinion and Statistics. Interviewers were trained at the CIDI [70] in the Federal University of São Paulo, an accredited center by the World Health Organization (WHO). Training procedures were conducted in accordance to the guidelines set up by the WHO. Interviews were carried out in the participants households by means of printed questionnaires. All questionnaires were translated into Portuguese and adapted to the local social and cultural context. Inclusion and exclusion criteria for the three case-control studies are described in tables 1 and 2, respectively. Individuals who met inclusion criteria during the epidemiologic study were invited to participate in the case-control study. Subjects exposed to traumatic life experiences resulting in PTSD (cases) will be compared to resilient subjects victims of traumatic life experiences without PTSD (controls) aiming to identify biological variables that might protect or predispose to PTSD. This case-control design will enrol representative subjects from the community being this procedure an important technique to overcome Berkson bias. Subjects will be informed about the procedures of the studies and will be asked to formally consent willingness to participate. Subjects who consent to participate in the case-control studies will receive the following assessment:

**Table 1 T1:** Inclusion criteria for PTSD cases (p) and control (c) groups

	Neuropsychological Study		Structural Neuroimaging study		Molecular Neuroimaging study	
	p	C	P	c	p	c
Age between 18 and 60 (inclusive)	X	X	X	X	X	X
Life time history of traumatic life experience as defined in criteria A of DSM IV criteria for PTSD	X	X	X	X	X	X
PTSD diagnosis according DSM IV criteria as assessed by SCID I applied by trained psychiatrists or psychologists	X		X		X	
Good general health with no additional diseases expected to interfere with the study	X	X	X	X	X	X
Able to understand and signed informed consent	X	X	X	X	X	X
Completed 5 years grades of education	X	X				
						
Fluent in Portuguese	X	X	X	X	X	X
Willing and able to complete all assessments	X	X	X	X	X	X
Willing to undergo neuroimaging (MRI)			X	X		
Willing to undergo neuroimaging (SPECT)					X	X

**Table 2 T2:** Exclusion criteria for PTSD cases (e) and control (c) groups

	Neuropsychological study		Structural Neuroimaging study		Molecular Neuroimaging study	
	
	p	c	p	c	P	c
Any significant neurologic disease, such as Parkinson's disease, multi-infarct dementia, Huntington's disease, normal pressure hydrocephalus, brain tumor, progressive supranuclear palsy, seizure disorder, subdural hematoma, multiple sclerosis, or history of significant head trauma followed by persistent neurologic defaults or known structural brain abnormalities.	X	X	X	X	X	X
Any significant systemic illness or unstable medical condition	X	X	X	X	X	X
History of significant head trauma followed by loss of consciousness			X	X		
Presence of pacemakers, aneurysm clips, artificial heart valves, ear implants, metal fragments or foreign objects in the eyes, skin or body.			X	X		
Claustrophobia			X	X		
Current use of psychoactive medications such as antidepressants, neuroleptics, anxiolytics or sedative hypnotics and mood stabilizers.			X	X	X	X
History of the following psychiatric disorders: schizophrenia, schizoaffective disorder, delusional disorder, bipolar affective disorder and depressive disorder with psychotic features (DSM IV criteria)	X	X	X	X	X	X
Tremor or dystonia in the cephalic region that unable the scanning procedure for imaging acquisition			X	X	X	X

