**Methods and design:**

Cases and controls will be identified through an epidemiologic survey conducted in the city of São Paulo. Subjects exposed to traumatic life experiences resulting in posttraumatic stress disorder (cases) will be compared to resilient victims of traumatic life experiences without PTSD (controls) aiming to identify biological variables that might protect or predispose to PTSD. In the neuropsychological case-control study, 100 patients with PTSD, will be compared with 100 victims of trauma without posttraumatic stress disorder, age- and sex-matched controls. Similarly, 50 cases and 50 controls will be enrolled for the structural study and 25 cases and 25 controls in the functional neuroimaging study. All individuals from the three studies will complete psychometrics and a structured clinical interview (the Structured Clinical Interview for DSM-IV and the Clinician-Administered PTSD Scale, Beck Anxiety Inventory, Beck Depression Inventory, Global Assessment of Function, The Social Adjustment Scale, Medical Outcomes Study 36-Item Short-Form Health Survey, Early Trauma Inventory, Clinical global Impressions, and Peritraumatic Dissociative Experiences Questionnaire). A broad neuropsychological battery will be administered for all participants of the neuropsychological study. Magnetic resonance scans will be performed to acquire structural neuroimaging data. Single photon emission computerized tomography with [(99m)Tc]-TRODAT-1 brain scans will be performed to evaluate dopamine transporters.

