Although molecular imaging allows reliable information on in vivo dopaminergic function [68], no studies, to our knowledge, has examined dopaminergic system activity in PTSD patients using molecular neuroimaging techniques.

The main reasons that justify such an effort to understand the problem of violence and its consequences for mental health can be described as follows: 1) Treatment strategies to be sponsored by the Brazilian public health care system need to be based on solid local data on the extent and nature of the disorder; 2) Exposure to traumatic life events is related to not only with mental disorders which include PTSD and depression, but also with other cognitive and neurotransmission dysfunctions [18,19,44,69]. The impact in mental health of the population of exposure to violence among the population of Sao Paulo, a large urban centre in a Middle Income Country (MIC), as well as specific parameters such as neurocognitive, neurostructural anf functional neuroimaging finds is virtually unknown.

The subjects of the study will be selected from an epidemiological/genetic survey in the city of Sao Paulo to assess the relationship between exposure to violence and the prevalence of PTSD and common mental disorders. Subjects located in the epidemiological/genetic survey will be referred to these three case-control studies, reported here, and to a randomized controlled clinical trial on the efficacy of topiramate for the treatment of PTSD symptoms.

This protocol is the result of collaborative task force to conduct translational research in the field of traumatic stress in urban regions of Brazil. The current project investigates possible causes for neurocognitive deficits, neurostructural changes and dopaminergic dysfunction in individuals with PTSD. We will be comparing individuals with current or lifetime diagnosis of PTSD with those who were exposed to a traumatic event but did not develop a current or a lifetime diagnosis of PTSD.

The main objectives of this project are:

1. to examine cognitive functioning of PTSD subjects and its relationships with symptomatology;

2. to evaluate neurostructural integrity of orbitofrontal cortex and hippocampus in PTSD subjects;

3. to evaluate if patients with PTSD have decreased dopamine transporter density in the basal ganglia as compared to resilient controls subjects.

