#### Data management and Analyses

1) Questionnaires will be double typed and data will be entered on SPSS software data files. Participants will be divided into two categories, according to the diagnosis: (1) lifetime diagnosis of PTSD and (2) Traumatic experience, but no lifetime diagnosis of PTSD. The following comparisons will be carried out in the two groups:

1) Neuropsychological Study: neuropsychological measures of PTSD cases compared to controls;

2) Magnetic resonance imaging study: to assess neurostructural abnormalities in OFC and hippocampus of patients with PTSD compared to resilient controls;

3) Molecular neuroimaging study: dopamine transporter density using single photon emission tomography of PTSD cases compared to controls.

Data will be codified and analyzed using the Statistical Package for Social Sciences (SPSS for Windows, version 15.0). Proportion differences will be compared using the Chi Square test or Fisher's exact test, as appropriate. Continuous variables will be compared by Analysis of Variance (ANOVA) or Mann-Whitney test for non-parametric data. All significant tests will be considered as 2-tailed. P values < 0.05 will be considered statistically significant. Because of the exploratory nature of the study, we do not consider alpha adjustment in multiple comparisons and we did not calculate the sample size (Table 3). The main analyses will examine the relationship between exposure to traumatic events and the PTSD occurrence. Unadjusted relative risk for studied variables cognition, cortisol level, hippocampal volume, and dopamine transporter density (and 95% confidence intervals) are presented for trauma without PTSD and trauma with PTSD, both with and without adjustment for age (18–29 years, 30–39 years, 40–49 years, 50–60) and gender. As a secondary analysis, we will be adjusting for clinical and demographic variables previously associated with PTSD: marital status, country of birth, socio-economic status, urbanicity and employment status.

**Table 3 T3:** Sample size in each study for PTSD cases and control groups

	Neuropsychological study		Structural Neuroimaging study		Molecular Neuroimaging study	
	
	Case	Control	Case	Control	Case	Control
Number of individuals for each group	100	100	60	60	25	25

PTSD = Posttraumatic stress disorder; MRI = Magnetic Resonance Imaging

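### Education is only an entry floor in the neuropsychological study and is neither matched nor adjusted for, so a schooling difference between cases and controls could appear as a PTSD-related cognitive deficit

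*Protocol article*

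**What the plan says.** **Eligibility.** Table 1 (Sample) has the criterion "Completed 5 years grades of education", ticked for cases and controls of the neuropsychological study only. It is a minimum, with no upper limit and no strata.

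**Matching.** The abstract (Methods and design) describes the comparison group as "100 victims of trauma without posttraumatic stress disorder, age- and sex-matched controls".

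**Analysis.** Under Data management and Analyses, "Continuous variables will be compared by Analysis of Variance (ANOVA) or Mann-Whitney test for non-parametric data", with no covariate stated. The relative-risk analyses, which count cognition among the studied variables, are planned "both with and without adjustment for age (18–29 years, 30–39 years, 40–49 years, 50–60) and gender". A secondary analysis adds "marital status, country of birth, socio-economic status, urbanicity and employment status". The Discussion says that depression measures should be covariates. None of these places mentions education.

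**Source.** "Cases and controls will be identified through an epidemiologic survey conducted in the city of São Paulo".

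**The concern.** Applying a schooling threshold only where the outcomes are test scores suggests that the authors regard schooling as relevant to those scores. A floor trims the lower tail but does not balance the groups: above it, one group can still have more schooling than the other.

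The Background makes a difference plausible. It lists cognitive ability, child abuse and general childhood adversity among pre-trauma risk factors for PTSD, and these may go with shorter schooling. That link is an inference, since the article does not name schooling as a risk factor.

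The first objective, cognitive functioning in PTSD, rests on this case-control comparison. The Discussion presents a better controlled sample as the way to resolve discrepancies in the literature. If the groups differ in schooling, the printed plan has no direct means of separating that difference from an effect of PTSD. The exposure recurs over about nine cognitive tests, with no adjustment for multiple comparisons.

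**Working it through.** The article states that no sample size was calculated, so there is no figure of the plan's own to reproduce. The check asks how large the problem could be.

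**Inputs from the article:** 100 cases and 100 controls, two-sided tests, significance at p<0.05.

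**Assumed inputs, not in the article:** education gap g of 0.2 to 0.5 SD, with cases lower; within-group correlation r between education and a test score of 0.4 to 0.6; no true PTSD effect. A milder case with r = 0.3 is also shown.

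**Step 1, spurious difference.** With unit SD, d = g × r. The range runs from 0.2 × 0.4 = 0.08 to 0.5 × 0.6 = 0.30 SD.

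**Step 2, chance of p<0.05 in the unadjusted comparison.** A two-sided t-test on 198 degrees of freedom has noncentrality d × √(100/2), that is, 7.07 × d.

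| g | r | d | Chance of p<0.05 |
|---|---|---|---|
| 0.2 | 0.3 | 0.06 | 7.1% |
| 0.2 | 0.4 | 0.08 | 8.7% |
| 0.3 | 0.5 | 0.15 | 18.4% |
| 0.5 | 0.5 | 0.25 | 42.1% |
| 0.5 | 0.6 | 0.30 | 56.0% |

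For scale, the difference detectable with 80% power at 100 per group is (1.96 + 0.84) × √(2/100) = 0.40 SD.

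**Step 3, socio-economic status as a partial proxy.** Suppose it correlates ρ with education and carries the group gap only through education. Adjusting for it then leaves d × (1 − ρ²). For g = 0.5 and r = 0.5:
- ρ = 0.4: 0.25 × 0.84 = 0.21 SD, about 32%.
- ρ = 0.6: 0.25 × 0.64 = 0.16 SD, about 20–21%.

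These keep the residual SD at 1, and both values of ρ are assumptions.

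**Step 4, effect of the fix.** In a simulation with 8,000 replicates per scenario and 100 per group, the unadjusted test was compared with ANCOVA on education.

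| g | r | Unadjusted | With education |
|---|---|---|---|
| 0.2 | 0.3 | 7.4% | 5.0% |
| 0.3 | 0.4 | 13.0% | 5.0% |
| 0.5 | 0.5 | 41.8% | 4.8% |
| 0.8 | 0.6 | 92.5% | 5.0% |

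The last row lies outside the assumed range and serves only as a stress case. With no gap at all, the covariate would still remove r² = 16% to 36% of the residual variance at r = 0.4 to 0.6.

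**The case against.** **No education gap is documented.** This is true. A reader might infer that the study will mistake schooling for a PTSD effect. The article supports only that it could, and with a small gap and a weak correlation the error rate stays near nominal, at about 7%.

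**The printed covariate list may not be complete.** The Discussion calls for depression as a covariate although the analysis section omits it, and an article condenses a fuller protocol. This limits the point but does not remove it. The article names its matching factors and two adjustment sets variable by variable, and education is in none of them.

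**Socio-economic status may cover education.** It is not defined, so it cannot be ruled out as a partial proxy, and dismissing it outright would go too far. It enters only the secondary analysis, however, and under the assumed correlations it leaves error rates well above 5%.

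**Adjustment has a cost.** The design seeks variables that protect against or predispose to PTSD. If education partly reflects pre-trauma ability, adjusting for it may remove some of that signal. Early PTSD may also have shortened schooling. Both stand, and they are reasons to show both results.

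**Urbanicity.** A reader might infer that it cannot vary in a one-city sample and that listing it is an error. The article does not define it. As current residence it would be nearly constant, but as place of upbringing or density within the city it could vary. A constant covariate drops out of the model and biases nothing.

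**Conclusion.** The point holds as a weakness in a list that the article prints. Education is recognised at entry and then left out of the matching and of both adjustment sets, so the comparison behind the first objective is open to confounding by schooling. What is established is the omission; a bias in the results is possible but not shown. The range of about 9% to 56% per test describes the unadjusted comparison and depends on the assumed gap and correlation, neither of which the article supplies. It also assumes no true PTSD effect and 100 per group. The secondary adjustment for socio-economic status could lower these figures by an amount that cannot be determined from the article. Because the remedy is cheap and can be fixed before the groups are compared, the change should be made.

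**What to change.** 1. Add years of completed education as a prespecified covariate in the case-control comparison of the cognitive scores. Use ANCOVA, or a rank-based or transformed equivalent where the Mann-Whitney test is planned.
2. Report each comparison with and without education, and state why: education may partly reflect pre-trauma ability or may have been shortened by early PTSD.
3. Confirm that the adapted CIDI sociodemographic form records years of schooling. The article does not list its items. Schooling must in any case be ascertained to apply the entry floor.
4. Define urbanicity, for example as place of upbringing, or drop it if it means current residence.

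The cost is one covariate, a second column of results and a few words in the analysis section. If the form records only whether the threshold was met, one further question is needed. The possible over-adjustment is made visible by the two sets of results.

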### Molecular imaging of dopamine transporter in PTSD

Physiological response to stressful experience involves a vast neural-endocrine-immunologic reaction that leads to the release of catecholamines and autonomic nervous system stimulation [57]. Noradrenergic and hypothalamus-pituitary-adrenal axis systems are the most common studied in response to stress [58] but many other neural-chemical systems are implicated. In animal studies, dopaminergic innervation of the basolateral nucleus of the amygdala, the medial prefrontal cortex and other limbic regions is highly responsive to stress and may be altered by stress [59-61]. Also the enhancement of the acoustic startle response, which can be a symptom of PTSD, has been related to the dopamine D1 receptor agonists in rats [62]. Genetically determined alterations in dopamine release and dopamine receptor expression in mice have been implicated in behavioral abnormalities induced by chronic stress [63]. This finding was interpreted as suggesting that stress-induced alterations of central dopaminergic neurotransmission may be genotype-dependent and expressed in behaviour. Human studies showed that there was a relationship between urinary excretion of dopamine and plasma dopamine and (the severity of) PTSD symptoms [64].

Evidence from genetic studies has proposed that reduced density of D2 dopaminergic receptor predisposes to PTSD [65]. There are two important PTSD candidate genes that directly affect the dopamine system: the dopamine receptor gene (DRD2) and the dopamine transporter (DAT) gene. The D2 dopamine receptor (DRD2) minor (A1) allele DRD2 A1 has already been linked to ADHD, Tourette's syndrome, conduct disorder and substance abuse [66]. This prompted suppositions that this gene may be involved in stress response in humans [61]. Polymorphism of the dopamine transporter (DAT) gene, in the locus SLC6A3 3' (VNTR), has been found to predispose to PTSD and to chronic forms of the disorder [67]. Taken together, these evidences suggest a relevant role for dopamine in the pathogenesis of PTSD.

To gain more clarity about any link between PTSD and the DAT, it is therefore important to clearly document PTSD patients, controlling confounders as alcohol consumption, major depression and clinical illness, through a functional neuroimaging investigation.

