#### SPECT scans of Dopamine Transporter

The kits of TRODAT-1 were obtained through a scientific collaboration with the Research Institute of Nuclear Energy, Lung-Tan, Taiwan. The metastable technetium-99 was produced by a generator of [99Mo] (molybdenum-99) from the Institute of Nuclear Energy Research (IPEN-SP) with freshly elution. The kits of TRODAT-1 were marked with [99mTc] according to the technique developed by Kung et al[94]. Sixty mCi of elution of Sodium Pertechnetate [99mTc] diluted in 5 ml of saline solution are injected in the kit and submitted to 16 atmospheres and temperature of 120°C, during 30 minutes in an autoclave. Later, the solution of [99mTc] TRODAT-1 is cooled at room temperature.

The images will be acquired through a single photon emission computerized tomography (SPECT) Gama camera of the type (Hawkeye General Electric Medical System, USA) according to the methodology previously validated [95]. All subjects will receive an intravenous injection of 2 ml containing among 22 to 25 mCi of [99mTc]-TRODAT-1 in an antecubital peripheral vein. Images will be acquired 4 hours after the injection. The SPECT modality of the system with two heads and fan-beam collimators of ultra-high resolution will be used. Energy Window will be 140 ± 14 keV and matrix of 128 × 128 in circular orbit with step and shoot movements of 64 steps for each head will be used, with diameter and degree of rotation of 30 cm and 360°, respectively. The time of acquisition for the projection will be of 20 seconds, with a factor of zoom of 1.45. The reconstruction of the SPECT images will be accomplished through a filter algorithm of filtered retroprojection and a Butterworth filter of 0.4 cut off with pixels of 10th order. Three-dimensional images of the whole brain will be obtained and, for the analysis, two transaxial slices will be used at the level of the striatal body, with 3 mm of thickness corresponding to the level of the largest captation of the radiotracer. DAT density will be calculated with binding potential (DAT-BP) using regions of interests (ROI) bilaterally drawn in the striatum (STR) and the occipital cortex (OCC-background). BP will be calculated with the formula striatum (STR-OCC)/OCC.

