## Discussion

This study protocol illustrates a collaborative work of potential value to researchers interested in innovative and realistic investigation aimed at understanding the neurobiology of PTSD in a population-representative sample. This article describes the methodological responses to challenges in conducting translational research, where patients are identified from a real-world scenario in a population-based study and go through neuropsychological, neurostructural and molecular neuroimaging techniques.

A recent review of the literature found over 60 studies examining memory and attention performance in PTSD subjects, but few studies have examined learning, executive functioning, and emotional reaction in this population. A key aim of the present neuropsychological study is not only to assess those less explored domains but, also, try to clarify some discrepancies reported in literature by examining a more homogeneous, adequately controlled sample. Some inconsistencies in neuropsychological findings may be attributed at least in part to sample limitations. Neuropsychological deficits involving attention and memory have been replicated in different samples including war veterans [14,15,20], rape victims, and other traumatized populations. However, most neuropsychological studies of PTSD involve war veterans with chronic PTSD who frequently exhibit comorbid psychiatric conditions such as depression, anxiety and substance use disorders, which represent major confounders [15]. The effects of depressed mood on neuropsychological functioning have been well documented [96]. The high rate of comorbidity and overlap of symptoms between these two disorders, however, makes it difficult to exclude individuals with current depression from PTSD studies. Therefore, it is important to address the presence of comorbid depression and to include measures of depression as covariates in analyses.

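### The SPECT eligibility rules cover psychoactive medication but not recent non-prescribed stimulant use, which could make a dopamine-transporter scan read falsely low

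*Protocol article*

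**What the plan says.** The Sample section refers the reader to Tables 1 and 2 for the eligibility criteria of all three studies. The drug row of Table 2 is ticked for cases and controls in both imaging studies. It excludes people currently taking psychoactive medications, "such as antidepressants, neuroleptics, anxiolytics or sedative hypnotics and mood stabilizers". The psychiatric row is limited to "schizophrenia, schizoaffective disorder, delusional disorder, bipolar affective disorder and depressive disorder with psychotic features (DSM IV criteria"; it does not mention substance abuse or dependence.

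The section on SPECT scans states that "DAT density will be calculated with binding potential (DAT-BP) using regions of interests (ROI) bilaterally drawn in the striatum" and the occipital cortex, and that "BP will be calculated with the formula striatum (STR-OCC)/OCC". It describes no drug question, screen or drug-free interval before the scan.

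The third objective is "to evaluate if patients with PTSD have decreased dopamine transporter density in the basal ganglia as compared to resilient controls subjects". The background to that objective speaks of "controlling confounders as alcohol consumption, major depression and clinical illness, through a functional neuroimaging investigation". The Discussion, writing of war-veteran samples in neuropsychological studies, refers to "comorbid psychiatric conditions such as depression, anxiety and substance use disorders, which represent major confounders".

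**The concern.** The outcome is the striatal signal in excess of background, relative to background, and the article treats it as transporter density. That reading holds only if nothing else occupies the transporter at the time of the scan. Cocaine and amphetamines act at this transporter. After recent use the ratio reflects the transporters still available to the tracer, so it reads low whatever the true density.

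A low reading is what objective 3 looks for. If recent use is commoner among cases, a few affected scans push the contrast towards the hypothesis in a study of 25 per group. The rule as drawn would admit those scans and count them as valid.

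**Working it through.** **Text check.** Could any stated rule catch a recent non-prescribed stimulant user in the molecular study?

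| Place in the article | Covers it? |
|---|---|
| Table 2, drug row | No. It reaches medications only; prescribed stimulants fall under the open list |
| Table 2, psychiatric row | No. Psychotic and bipolar disorders only |
| Table 1, general-health row | No. It concerns diseases; occasional use is not one |
| Clinical assessment, SCID-I | It can diagnose a disorder, but no substance diagnosis excludes anyone, and a diagnosis does not date the last use |
| SPECT section | No question, screen or interval |
| Analysis section, covariates | Age and gender, then five social and demographic variables; no substance term |

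The article itself treats substance use as a problem in three places: as a potential confounder under the neuropsychological findings, as a major confounder in the Discussion, and again in the Discussion as a rival explanation for structural and cognitive findings.

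**Size.** The article gives no binding-potential spread, no rate of use and no sample size calculation, so there is no figure to reproduce. What follows is illustration.

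*From the article:* 25 cases and 25 controls; two-sided test at 0.05.

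*Assumed:* no true difference; normal binding potential scaled to mean 1; coefficient of variation (CV) 15-25%; an affected scan loses 20-50% of its signal.

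With k1 affected cases and k0 affected controls, the false fall in the case mean relative to controls is (k1 − k0)/25 × loss. In SD units, divide by the CV.

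- 2 v 0, 50% loss: 2/25 × 0.50 = 4%; at CV 15%, 0.04/0.15 = 0.27 SD.
- 3 v 0, 50% loss: 3/25 × 0.50 = 6%; at CV 15%, 0.06/0.15 = 0.40 SD.
- 2 v 0, 20% loss: 2/25 × 0.20 = 1.6%; at CV 25%, 0.016/0.25 = 0.06 SD.
- 3 v 1, 50% loss: (3 − 1)/25 × 0.50 = 4%.
- Equal numbers: 0%.

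For comparison, the difference detectable with 80% power is (1.960 + 0.842) × √(2/25) = 0.79 SD.

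Simulation (two-sample t-test, 40,000 replicates, CV 15, 20 and 25%, loss 20, 30 and 50%) gives the chance of p < 0.05 with cases lower:

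| Affected scans, cases v controls | Chance |
|---|---|
| 0 v 0 | 2.5% |
| 2 v 0 | about 4-8% |
| 3 v 0 | about 5-14% |
| 2 v 1 | about 2-3% |
| 3 v 1 | about 4-5% |
| 2 v 2 | about 0.3-2% |

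Affected scans also inflate the variance, which offsets part of the mean shift. That is why one affected control removes most of the inflation, and why equal numbers make the test conservative.

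These rates are for fixed counts. If the counts vary by chance around underlying rates of 12% in cases and 4% in controls (3 and 1 expected), the same simulation with random counts gives about 4-10%. With 4% in both groups it stays at 2.5%.

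**Can the group contrast be repaired?** With 3 v 1 affected scans, 50% loss and CV 15%, adding an indicator for recent use to the model returns the chance to 2.5%. This needs use to have been recorded.

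**The case against.** Several points against the concern are sound.

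- *Prescribed stimulants.* A reader might infer that the drug row leaves them out because the named classes do not include them. The classes are examples, and a prescribed stimulant is a psychoactive medication, so the row excludes it.
- *The word for current use.* A reader might infer that someone who took such an agent just before the visit escapes the rule. On an ordinary reading that person is a current user. The difficulty is that the row concerns medications, not that it fails to define current.
- *Adjustment.* A reader might infer that no analysis could rescue the comparison. An indicator for recorded use restores the group contrast, although it does not make the individual scan valid.
- *Size.* The larger false-positive figures, up to 14%, need three affected cases, no affected control and a 50% loss. Cases and controls come from one community survey, so no use at all among controls is an extreme assumption.
- *Mechanism.* Transporter occupancy is outside knowledge; the article does not discuss it.
- *Condensed report.* An article may leave scan-day procedures to the full protocol, and this one calls itself exploratory.

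The last point does not dispose of the matter. The article presents Tables 1 and 2 as the eligibility criteria and includes a drug row drawn for this study. The objection is to where that row stops, not to missing operational detail.

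**Conclusion.** The gap is real but narrow. As written, a person who has recently used a non-prescribed stimulant is eligible for the SPECT study, and the scan counts as a measure of transporter density. Such a scan would read falsely low, given the pharmacology stated above.

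Bias towards objective 3 needs more recent use in cases than in controls. The article's own remarks on substance use make that plausible, but they concern neuropsychological and structural work, partly in war veterans, and give no rates for this population. With equal use the effect is added variance and lost power, not a false finding in the hypothesised direction.

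Under the assumptions shown, a false lower-in-cases result has a chance between roughly 2% and 14%, against a nominal 2.5%. The upper end belongs only to the case with no affected controls and the largest loss. The documents do not support a claim that the SPECT result would be uninterpretable; they support a cheap correction that should be made.

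**What to change.** In the molecular-study columns of Table 2, add an exclusion for recent non-prescribed use of substances that act on the dopamine transporter, with the interval set by the study's nuclear medicine team. Ask about such use on the day of the scan, in the same words for cases and controls, and record the answer. State in the analysis section that affected scans are omitted from the dopamine-transporter comparison, or that the comparison is adjusted with the recorded-use indicator, and choose between the two before the data are seen. This is an eligibility screen and asks no one to change a treatment.

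The cost is one table row, one sentence in the analysis section and a short checklist. A few otherwise eligible participants will be lost from a group of 25, and self-report is imperfect, so some affected scans may remain.
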